**Table pone.0332773.t004:** 

ED readmissions	Number of ED visits since the initial visit
**Falls**	Number of falls since the initial visit
**Delirium incidence**	Assessed using the Family Confusion Assessment Method (FAM-CAM) [29] administered to a family member or caregiver
**Mood**	Assessed using the GDS-15
**Quality of life**	Assessed using the EQ-5D
**Functionality**	Assessed using the Katz Index, Barthel Index, and Lawton Scale
**Cognitive performance**	Assessed using the 10-CS
**Mortality**	If the patient has passed away, the date and cause of death will be recorded

#### Chart review and administrative data.

Length of hospital stay and hospital costs will be extracted from the electronic medical record and HSL’s Business Intelligence (B.I.) administrative databases.

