**Methods:**

This study protocol outlines a before-and-after study to evaluate the impact of implementing a comfort menu and cart on the experience and outcomes of older patients treated in the ED. The study will be conducted in the ED of Hospital Sírio-Libanês (HSL), a tertiary private hospital in São Paulo, Brazil. Patients aged 65 and older who presented to the ED will be eligible for inclusion. Participants will be recruited in two phases: pre-intervention and post-implementation of the comfort menu and cart. Data will be collected through patient and staff interviews, chart reviews, and a 30-day follow-up interview. Patient experience, staff experience, length of hospital stays, hospital costs, ED readmissions, falls, delirium incidence, quality of life, functional status, cognitive performance, and mortality will be assessed.

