#### Exclusion criteria.

Decline to participate in the study or use the comfort menu and cart.Absence of a companion able to consent to study participation and provide necessary information for patients with altered mental status or cognitive impairment.Decreased level of consciousness.Hemodynamic instability.Acute respiratory failure.Inability to be contacted by phone for the follow-up interview.

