**Table pone.0332773.t002:** 

Demographics	Full name, medical record number, ED visit number, date of birth, postal code, sex, date and time of ED admission
**Source of information**	If not the patient, the source’s full name, date of birth, sex, and relationship to the patient will be recorded
**Sensory deficits**	Presence and type of visual and/or hearing impairments
**History of falls**	Number of falls in the past year, circumstances surrounding the falls
**Comorbidity**	Assessed using the Charlson Comorbidity Index (CCI) [12–15]
**Risk of falls**	Assessed using the Memorial Emergency Department Fall Risk Assessment Tool (MEDFRAT) and the Carpenter instrument [16,17]
**Frailty**	Assessed using the Clinical Frailty Scale (CFS) version 2.0 [18,19]
**Clinical severity**	Assessed using the National Early Warning Score (NEWS) 2 [20,21]
**Mood**	Assessed using the 15-item Geriatric Depression Scale (GDS-15) [22]
**Geriatric vulnerability**	Assessed using the PRO-AGE Score [10]
**Acute mental status change (delirium)**	Assessed using the Delirium Triage Screen (DTS) and Brief Confusion Assessment Method (bCAM) [23]
**Quality of life**	Assessed using the Euro Quality of Life Instrument – 5D (EQ-5D) [24]
**Functionality**	Assessed using the Katz Index, Barthel Index, and Lawton Scale [25–27]
**Cognitive performance**	Assessed using the 10-Point Cognitive Screener (10-CS) [28]

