#### Follow-up interview.

A second research assistant, blinded to the initial assessment and ED care details, will conduct a phone interview 30 days (± 2 days) post-initial assessment. This interview will assess the following:

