### Data management and statistical analysis

All study data will be collected and managed using Research Electronic Data Capture (REDCap) [30], a secure web-based application. Research assistants will use tablets with online access to the REDCap database for direct data entry and informed consent procedures.

For the primary objective evaluating the impact of the comfort menu and cart on the experience of older patients we will use the questionnaire adapted from Lichen et al. (2021) and McCusker et al. (2018). For the secondary objectives evaluating the impact of a comfort menu and cart on the experience of medical and multidisciplinary staff involved in caring for older patients treated in the ED, we will use the the questionnaire adapted from Lichen et al. (2021).

Data analysis will be performed using Stata version 17 (StataCorp, College Station, TX). All statistical tests will be two-tailed with an alpha error of 0.05. Numerical variables will be reported as means and standard deviations or medians and interquartile ranges (IQR) depending on their distribution, which will be assessed visually and using the D’Agostino-Pearson test for normality. Categorical variables will be described as absolute counts and proportions. Numerical variables will be compared using Student’s t-test or ANOVA for normal distributions and Wilcoxon or Kruskal-Wallis tests for non-normal distributions. As appropriate, categorical variables will be compared using the chi-square test or Fisher’s exact test. Analyses will be adjusted to account for potential confounding variables, such as baseline frailty, cognitive impairment, and clinical severity. Missing data will be handled though mixed effects model.

All relevant data from this study will be made available upon study completion.

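### ED revisits and deaths rest on one 30-day phone call, although the hospital record could supply those seen at this hospital for every enrolled patient

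*Protocol article*

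**What the plan says.** Under Follow-up interview, a second research assistant "will conduct a phone interview 30 days (± 2 days) post-initial assessment". The table in that section lists ED readmissions, defined as "Number of ED visits since the initial visit", and mortality: "If the patient has passed away, the date and cause of death will be recorded".

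Under Chart review and administrative data, the article states: "Length of hospital stay and hospital costs will be extracted from the electronic medical record" and the hospital's Business Intelligence databases. Revisits, admissions after the index visit and deaths are not named there.

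Three other places bear on the point:

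- The data table under Initial interview collects "Full name, medical record number, ED visit number, date of birth", so each participant can be linked to the hospital record.
- Exclusion criteria includes "Inability to be contacted by phone for the follow-up interview".
- Data management and statistical analysis says "Missing data will be handled though mixed effects model".

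The abstract mentions chart reviews only as a general source: "Data will be collected through patient and staff interviews, chart reviews, and a 30-day follow-up interview".

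**The concern.** Patients who have died, are in hospital or have declined cognitively are plausibly the hardest to reach by phone. They are also plausibly the likeliest to have had a revisit or to have died. If so, non-contact is related to the outcome, and rates based on completed calls come out too low.

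The two phases are not randomised and run one after the other. A difference in contact rates between them would therefore show up as a difference in revisits or deaths and could be read as an effect of the comfort cart.

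Among patients who are reached, the revisit count depends on the recall of older people, some of them cognitively impaired, or of a companion.

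Readmissions are named in the secondary objectives and in the expected results, and the Discussion presents the 30-day outcomes as a new contribution of this study. Revisits and deaths at this hospital could be read from a source the trial already plans to query.

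**Working it through.** **Sources side by side**

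| Outcome | Named source | If nobody is reached |
|---|---|---|
| Length of stay, costs | Electronic record, administrative databases | Still available |
| ED readmissions | 30-day call | Missing |
| Mortality | 30-day call | Missing |

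No section names a second source for the last two rows.

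**Can the stated missing-data method help?** A mixed effects model borrows from repeated measurements. Mood, quality of life, function and cognition are measured at the initial interview and again at day 30, so a patient missing at day 30 still contributes a baseline value. The revisit count and vital status are each measured once. Without the call there is no other measurement of that outcome to borrow from.

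**Does the phone exclusion remove the problem?** The article does not say when it is applied. If at enrolment, a patient with a working number can still be missed at day 30. If at day 30, unreached patients leave the study altogether, possibly including some who died, which is worse.

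**Size.** From the protocol: 132 patients per phase, 264 in total. The protocol has no contact rate or event rate to reproduce, so the following inputs are assumptions: unreached share u, true event rate p, and risk ratio RR for unreached against reached patients.

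Patients without either outcome = 264 × u:

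- u = 5%: 13.2
- u = 10%: 26.4
- u = 20%: 52.8

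Observed rate among the reached = p / [(1 − u) + u × RR].

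- Revisits, p = 20%, u = 10%, RR = 2: 0.20 / (0.90 + 0.20) = 18.2%
- Revisits, p = 20%, u = 10%, RR = 3: 0.20 / (0.90 + 0.30) = 16.7%
- With RR = 1 the observed rate is 20%: no bias, only fewer patients

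Unequal contact, p = 20% in both phases, RR = 2:

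- Before, u = 5%: 0.20 / (0.95 + 0.10) = 19.0%
- After, u = 15%: 0.20 / (0.85 + 0.30) = 17.4%
- Apparent change: a fall of about 1.7 points where nothing changed

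Deaths, p = 5%, u = 10%, RR = 3:

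- Expected deaths: 264 × 0.05 = 13.2
- Rate in the reached: 0.05 / 1.20 = 4.17%
- Deaths captured: 264 × 0.90 × 0.0417 = 9.9, so about 3 of 13 are missed

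The death figure supposes that no relative reports a death among the unreached, so it is an upper figure for this set of assumptions.

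**The case against.** **The article is condensed.** It says two items will be extracted; it does not say that nothing else will be, and chart review is listed generally in the abstract. A full protocol could hold a longer field list. This has some weight. But the article goes beyond silence: it states the source of each outcome and places these two in the call. That assignment can be judged as it stands. That the record will be opened for every participant is a fair inference from the identifiers and the planned extraction, not a stated sentence.

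**Deaths do not need the patient to answer.** This stands. Companions may be informants, and the follow-up interview already includes a delirium instrument given to a family member or caregiver. A reader might infer that most deaths would be lost, but the documents do not support that. For example, suppose 2% mortality in one phase (132 × 0.02 = 2.64 deaths) and 15% unreached (19.8 patients). Losing two deaths would then mean 2 / 19.8 = 10.1% mortality in the unreached against 0.64 / 112.2 = 0.57% in the reached, a risk ratio near 18. That is far from the ratios of 2 to 3 used above.

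**The comparison may hardly change.** If the contact rate and risk ratio are equal in both phases, much of the bias cancels in the difference. The call procedure is the same in both phases, and unequal contact is a possibility, not something shown. The 1.7 points are also small beside sampling error: with 132 per phase and a rate near 17%, the 95% half-width for a difference is 1.96 × √(2 × 0.17 × 0.83 / 132), about 9 points. This stands and limits the priority. It does not remove the understatement of the rates within each phase.

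**The record is not a better measure of the planned outcome.** A reader might infer that record-based revisits should replace the phone count. The planned count is of ED visits without restriction to this hospital, and the record misses visits elsewhere. Replacement would exchange recall and non-contact error for under-capture. The record is justified as a supplement.

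**Conclusion.** The concern holds in a limited form. Revisits and deaths are tied to a single phone contact. Patients for whom nobody is reached contribute neither, and neither the mixed effects model nor the phone exclusion repairs this. With 5–20% unreached, about 13 to 53 of 264 patients would lack both outcomes. At 10% unreached and a risk ratio of 2 to 3, a true 20% revisit rate would be seen as about 17–18%. A 5% against 15% imbalance with a risk ratio of 2 would create a change of about 1.7 points. All contact rates, event rates and risk ratios here are assumed; only the sample size comes from the protocol.

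Readmissions are exploratory, and mortality is not named in the objectives. A reader might infer that the main result is at risk. It is not: the patient-experience questionnaire is completed at the initial interview and does not depend on the call, unless the phone exclusion were applied after enrolment. This is an inexpensive improvement of modest priority.

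**What to change.** Under Chart review and administrative data, extend the extraction to ED visits, admissions and deaths recorded at this hospital from the index visit to day 30, for every enrolled patient, whether or not the call succeeded.

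- **Readmissions:** keep the phone count of all ED visits as planned. Report record-based revisits to this hospital beside it, labelled as such, as the measure available for all participants.
- **Mortality:** combine the record with the report of the patient's contact or companion, counting deaths up to day 30.
- **Reporting:** give the number reached and not reached in each phase.

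The cost is a few more fields in an extraction already planned, using identifiers already collected. Recruitment is scheduled from April 2026 and data processing from November 2026, so the fields can be added in time. The sponsor should confirm that consent and ethics approval cover them. The remaining weakness is that the record misses visits and deaths elsewhere, which is why the phone data stay.

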### Intervention

The comfort menu and cart will be implemented after the pre-intervention data collection phase is completed. The menu will list the items available on the cart and will be presented to eligible patients in printed or digital format (on a tablet). The cart will be placed in an easily accessible area within the ED. Approximated retail prices have been previously reported [3].

A one-month dedicated rollout period will precede the commencement of post-intervention participant enrollment. This phase is designed for comprehensive staff training on the proper use and components of the comfort menu and cart, including familiarization with all available items and menu options. Additionally, this period will ensure all necessary equipment is adequately prepared and any potential logistical challenges associated with the cart’s implementation are identified and resolved, thereby optimizing the fidelity and effectiveness of the intervention before data collection for the post-intervention group begins.

Comfort Cart Contents:

Hot and cold packs;Extra blanket and pillow;Face towel;Gloves and hat;Personal hygiene kit (toothbrush, toothpaste, cotton swabs, sleep mask, comb, deodorant, hand lotion);Items for distraction (magazines, word search puzzles, playing cards, coloring pages);Items to enhance communication (reading glasses, magnifying glass, penlight, cell phone charger, notepad, sound amplification device).

Comfort Menu Options:

Physiotherapy assessment;Conversation with chaplain, concierge, or social worker;List of resources for older adults needing community services;Home care assistance.

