### Data collection

#### Recruitment.

A trained research assistant will recruit participants in the ED, working 25 hours per week (five 5-hour shifts between 10:00 am and 10:00 pm) over six months (three months pre-intervention, from April 2026 to June 2026, and three months post-intervention, from July 2026 to September 2026). The assistant will conduct active searches for potential participants. Eligible patients will be invited to provide informed consent.

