**Table pone.0332773.t005:** 

Year	2025												2026												2027					
**Month**	1	2	3	4	5	6	7	8	9	10	11	12	1	2	3	4	5	6	7	8	9	10	11	12	1	2	3	4	5	6
**Ethics committee and institutional submission and processing**	X	X	X	X	X	X																								
**REDCap project development**										X	X	X	X	X	X															
**Hiring and training of research assistant**										X	X	X	X	X	X															
**Pre-intervention case inclusion/ recruitment**																X	X	X												
**Intervention structuring – comfort cart (rollout period)**																		X												
**Implementation of the comfort cart**																			X	X	X									
**Post-intervention case inclusion/ recruitment**																			X	X	X									
**Follow-up interview**																	X	X	X	X	X	X								
**Data processing and statistical analysis**																							X	X	X	X				
**Preparation of reports and articles for publication**																											X	X	X	X

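### The one-month rollout with staff training has no recruitment-free month: it falls in June 2026, the last month of control recruitment

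*Protocol article*

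**What the plan says.** Three places in the protocol fix the calendar.

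- **Intervention.** "The comfort menu and cart will be implemented after the pre-intervention data collection phase is completed". The same section adds: "A one-month dedicated rollout period will precede the commencement of post-intervention participant enrollment". On content: "This phase is designed for comprehensive staff training on the proper use and components of the comfort menu and cart". The month also serves to prepare equipment and settle logistics.
- **Recruitment.** Enrolment takes six months: "three months pre-intervention, from April 2026 to June 2026, and three months post-intervention, from July 2026 to September 2026". There is no gap between the phases.
- **Timeline table (under Expected results).** The row "Pre-intervention case inclusion/ recruitment" is marked for April, May and June 2026. The rollout row has a single mark, in June 2026. The row "Implementation of the comfort cart" and the row for post-intervention recruitment are both marked for July, August and September 2026.

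The section on the staff interview has staff questioned at the same time as patients are recruited, so control-phase staff interviews also run through June. The document describes no separate handling of patients or staff interviewed in June, and the limitations in the Discussion do not mention the overlap.

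**The concern.** The study is an uncontrolled before-after comparison, so the contrast depends on a clean first period. In June, staff are to be trained on the cart, its items and the menu while they care for control patients. The patient questionnaire asks about comfort, about care fitted to communication, hearing and vision needs, and about whether staff did all they could to relieve discomfort. Training on those subjects could move the answers before the cart is in use.

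The staff survey is more directly exposed. Its control-phase items ask whether staff have drug-free means of comfort at hand and whether offering them adds too much work. In June these questions would go to people who are being trained on exactly those means.

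The likely result is a first period that already looks a little like the second, and so an understated difference. Once June controls are enrolled, this can be explored but not undone.

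**Working it through.** **1. Calendar.** The marks in the timeline table were counted against its 30 month columns (January 2025 = column 1).

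| Row | Columns | Months |
|---|---|---|
| Pre-intervention recruitment | 16–18 | April–June 2026 |
| Rollout | 18 | June 2026 |
| Implementation of the cart | 19–21 | July–September 2026 |
| Post-intervention recruitment | 19–21 | July–September 2026 |

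The dates in the Recruitment section agree with these rows, so a column displaced in text extraction does not explain the overlap. With phases back to back, any one-month rollout that directly precedes July has to lie inside control recruitment.

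**2. Share of controls.** One month of three is 132/3 = 44. By days it is 30/91 = 33.0%, or 132 × 30/91 = 43.5. Both assume an even recruitment rate. That leaves 132 − 44 = 88 controls from April and May.

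**3. The plan's own sample size.** The inputs are a difference of 0.98 on a 1–6 scale, 90% power, 5% significance and 132 per group (Sample size calculation), with two-tailed tests (Data management and statistical analysis). No SD is given, so 132 cannot be reproduced, only solved backwards:

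SD = 0.98 × √(132/2) / (1.960 + 1.282) ≈ 2.456, a standardised effect of 0.98/2.456 ≈ 0.40.

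The largest SD possible on a 1–6 scale is (6 − 1)/2 = 2.5. The back-solved value is therefore close to a ceiling, and smaller SDs have to be shown beside it.

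**4. Dilution.** Let Δ be the full effect and f the fraction of it that training alone gives to June controls. The control mean moves by (1/3) × fΔ, so the contrast becomes Δ(1 − f/3). This shrinks it by 8% at f = 0.25, 17% at f = 0.5, 25% at f = 0.75 and 33% at the upper bound f = 1.

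**5. Power after dilution.** Power = Φ( 0.98(1 − f/3) / (SD × √(2/132)) − 1.960 ). For f = 0.5 and SD 2.456: 0.817 / (2.456 × 0.1231) − 1.960 = 0.74, which gives 77%.

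| f | Difference | SD 2.456 (back-solved) | SD 2.0 (assumed) | SD 1.5 (assumed) |
|---|---|---|---|---|
| 0 | 0.98 | 90% | 98% | >99.9% |
| 0.25 | 0.90 | 84% | 95% | 99.8% |
| 0.5 | 0.82 | 77% | 91% | 99% |
| 0.75 | 0.74 | 68% | 85% | 98% |
| 1 | 0.65 | 58% | 76% | 94% |

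**6. Leaving June controls out.** The standard error grows by √[(1/88 + 1/132) / (2/132)] = √1.25 = 1.118, about 12%. Power for 88 against 132 at the full 0.98 is 82.6% (SD 2.456), 94.5% (SD 2.0) or 99.7% (SD 1.5).

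**The case against.** The strongest reply is that the sections can be read together. June does precede July. The table separates structuring the intervention (June) from implementing it (July to September). A dedicated month need not mean a month without recruitment. If training is not counted as implementation, recruiting in April to June, training in June and going live in July satisfies every sentence. This stands: the text does not strictly contradict itself. What remains is that staff training falls inside the control period.

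A reader might go further and infer that a third of the controls are contaminated. The documents do not support that. Nowhere are June patients said to be offered the cart or menu, and implementation starts in July. Much of the intervention consists of physical items, which training alone does not deliver. The overlap is certain; its effect is not.

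A reader might also take the fall in power to 68% as the expected cost. It rests on an f that has no basis in the documents and on an SD near the maximum of the scale. At SD 2.0 the same f leaves 85%.

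Finally, one might count the July follow-up of June controls as exposed because the cart is then live. That adds little: it is a telephone interview by an assistant blinded to ED care details, about patients whose index visit came before the cart.

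**Conclusion.** The concern holds as an overlap, not as demonstrated contamination. As scheduled, up to a third of controls (about 44 of 132, if recruitment is even) and the June control-phase staff interviews fall in the month of staff training. The risk is of unknown size, most direct for the staff survey, and most plausibly dilutes the difference toward zero, so it is unlikely to create a false positive.

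For patients, the shrinkage is f/3 with f unknown. It assumes that all June controls are exposed to the same degree and ignores any change in spread. At f = 0.5, power is about 77% at the back-solved SD, 91% at 2.0 and 99% at 1.5. Because the protocol states no SD, these figures are illustrative, and the scheduling point does not depend on them. It is worth correcting before the first control is enrolled.

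**What to change.** Reconcile the Recruitment section, the Intervention section and the timeline table by placing one recruitment-free month between the phases. For example:

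- controls April–June 2026, as planned;
- rollout and training in July, with no enrolment;
- post-intervention enrolment August–October, follow-up to November;
- data processing, which now starts in November, and all later rows moved by one month.

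State that staff training starts only after the last control patient and the last control-phase staff member have been interviewed.

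The cost is about one calendar month and a one-month break in the research assistant's recruitment schedule, with no extra participants. Bringing control recruitment forward to March–May is not a good alternative, because the table has REDCap development and the hiring and training of the assistant running through March 2026.

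If the dates cannot move, pre-specify a sensitivity analysis that leaves out June controls and June staff interviews. For patients this compares 88 with 132 and widens the standard error by about 12%. It shows whether the result depends on June but does not restore a clean control period.
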